### Analysis

The health-economic evaluation will be conducted as a CEA with health care costs (in euro for the reference year 2018) related to WHODAS treatment response (WHODAS functioning dichotomized) and a CUA of incremental costs per QALY gained. These analyses will be conducted from the health care system perspective and hence will have a focus on health care costs and health-related outcomes. Sensitivity analyses will be carried out and will be directed at the main cost drivers and uncertainty in the outcomes. Sensitivity analyses are conducted to assess the robustness of the main analyses of the CEA and CUA or to enrich the analyses by repeating them in a different way. In one of the planned sensitivity analyses, the CEA and CUA are expanding the health care system’s perspective to a wider societal perspective (with changes in productivity included). Finally, the statistical analyses will be based on the pooled dataset of all five trials. Owing to the lack of country-specific guidelines for each of the participating sites, the guidelines of the UK National Institution for Care Excellence will be used [15,16].

### Costing

Total costs will be estimated using a bottom-up (or microcosting) approach, where units of health service are multiplied by their appropriate unit cost price and summed to provide an overall total cost estimate [11]. Unit costs will be determined for Croatia and will be extrapolated to the other participating countries based on the purchasing power parity of the respective countries.
Cost prices will be estimated using microcosting based on hospital records, financial departments, and national tariffs. Microcosting takes into consideration (if applicable) the initial investment for equipment, other investments, maintenance, number of years of use and discounting, material costs, personnel costs (per hour), and an increase for the overhead of the respective unit price. Costs of medication (and dispensing costs) will be calculated using daily defined dosage (based on clinical practice guidelines) and data from the financial departments of the five participating hospitals, indicating the mean medication usage per adult a day. Productivity losses will only be included in the analyses in which a societal perspective is adopted. Productivity losses will be evaluated using both the friction cost approach (ie, calculation of productivity losses solely for a prespecified “friction period” in which an employee would have been replaced) and the human capital approach (ie, calculation of the productivity losses for the full period of absenteeism) [17,18]. Furthermore, costs of informal care will be based on the shadow prices for unpaid work in the respective countries. Costs of transport will be calculated as the mean distance per destination to the health care provider multiplied by tariffs of public transport. Total costs will be aggregated over time by calculating the area under the curve (AUC). All costs will be expressed in euro for 2018. If necessary, existing cost prices will be updated to 2018 values using the consumer price index.

All costs will be converted to Int.€ using purchasing power parity, which makes it possible to compare costs between countries with different standards of living (to derive a uniform currency by equalizing the purchasing power of different currencies through the elimination of differences in price levels between countries [19]). Following the National Institute for Care Excellence (NICE) guidelines for health-economic evaluation, both costs and effects will be discounted by 3.5% per annum, because the time horizon of the trials extends beyond 1 year. However, discounting rates will be subject to sensitivity analysis because discounting can have a substantial impact on the outcomes of a health-economic evaluation.

### Cost-Effectiveness Analysis

The CEA, with costs and WHODAS functioning as the primary outcomes, will be conducted in several steps.

First, WHODAS global functional disability will be computed using the scoring algorithm based on the item response theory as recommended by WHO [6]. This algorithm provides a per patient functional disability score between 0 and 100, with higher scores indicating greater disability.

Second, the sample characteristics at *t_0_* will be described to see if despite randomization, some baseline imbalances across conditions have occurred in prognostically relevant variables (ie, variables that are strongly correlated with the outcome). If this is the case, such variables will be used as covariates to make adjustments for the baseline imbalances. In the unlikely scenario where many potential confounders are found, covariate adjustments will be made more efficiently using inverse propensity score weighting, with w=1/p in the control group and w=1/(1-p) in the experimental group, where *w* is the weight and *p* is the propensity score (ie, the likelihood that a participant is in one condition rather than the other), and *p* will be estimated under a logistic model.

Third, dropout will be evaluated, and missing observations in WHODAS functioning at *t_1_* and *t_2_* will be imputed to permit ITT analysis. The imputation will be based on the predictors of outcome (for accuracy) and predictors of missing values (to adjust for possibly selective dropout). To handle missing data, single imputation using predictive mean matching embedded in nonparametric bootstraps of seemingly unrelated regression equations (SURE model) will be used. In a recent paper by Brand et al, single imputation nested in the bootstrap percentile method emerged as the method with the best statistical properties [20]. Predictive mean matching will be used to account for nonnormality of the data by imputing “real” observed values from similar cases instead of imputing regression estimates [21,22].

Fourth, in the context of the economic evaluation, WHODAS global functioning must be dichotomized into a binary treatment response outcome. This is done because from an economics perspective, it is meaningless to relate hard currency (euro, which is measured at the interval level) to a health gain (measured at an “elastic” ordinal measurement level). In other words, for a health-economic evaluation, a “tangible” outcome on par with the hard currency required to generate that health outcome is needed in order to merit a meaningful analysis. In this analysis, a binary *treatment response* variable (1, improved; 0, not improved) would constitute such a hard outcome. For the main analysis, treatment response is defined when a patient has improved by 0.33 standard units or more. A change of 0.33 standard units is equivalent to a 6-point change on the WHODAS 0-100 scale. Thus, when a patient has improved 6 points or more, the patient is considered as a treatment responder (ie, treatment response=1 or else 0).

Fifth, to simultaneously evaluate both costs and outcomes, SURE models will be used. The SURE models will be baseline adjusted with baseline WHODAS functioning and cost as covariates or weighted with inverse propensity scores as needed. Because costs are nonnormally distributed, the SURE models will be bootstrapped (2500 times). When bootstrapping, one creates N times (in this case 2500 times) a new sample out of the original sample with replacement. This results in N different samples. Incremental cost-effectiveness ratios (ICERs) will be computed by dividing the between-condition differences in costs by the difference in effects (treatment responders). Thereafter, the scatter of 2500 bootstrapped ICERs will be plotted on the ICER plane. When most simulated ICERs fall into the north-east quadrant of the ICER plane (indicating that better health is achieved at higher costs), an acceptability curve will be graphed for decision-making purposes. The acceptability curve depicts the likelihood that the new health care system has acceptable cost-effectiveness relative to CAU given varying willingness-to-pay ceilings for gaining a QALY [23].

These health-economic evaluations will answer the question, “To what extent the newly implemented community-based recovery-oriented health care system has better patient-level outcomes with regard to WHODAS functioning?”

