### Recruitment

Patients will be recruited from the population being treated by specialized inpatient and outpatient mental health services participating in the study. Eligible patients expressing interest to participate will receive an introductory letter, a patient information leaflet explaining the study’s aims and procedures, and an informed consent form. Patients willing to participate in the study will be asked to sign and return the informed consent form. Patients who decline participation in the study will receive CAU. Each included patient receives a unique identification number for data collection and monitoring of patient flow into and through the trial. At each site, a minimum of 180 patients and a maximum of 200 patients need to be recruited.

In line with ethical requirements, any study participant can decide to withdraw from the study at any time. In addition, responsible clinicians can decide for individual patients to deviate (temporarily or permanently) from the intervention program. Their professional autonomy and responsibility remain. Nonetheless, data analysis will be conducted in agreement with the intention-to-treat (ITT) principle, where all randomized participants are analyzed in the condition to which they were randomized.

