### Randomization and Masking

Eligible and consenting patients will be randomly allocated to either the intervention (receiving care provided by CMHTs) or usual care condition consisting of inpatient or outpatient mental health care (described above). An independent statistician, otherwise not involved in the trial, will carry out the randomization at each of the sites, with patients as the unit of randomization. Simple randomization with 1:1 allocation will be applied using a randomization website [5] for true random number generation. In this type of study (a hybrid implementation-effectiveness trial), it is not possible to conceal the randomization status from either clinicians or patients, and masking will therefore not be attempted.

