### Analysis of Pooled Trial Data

One of the secondary goals of the RECOVER-E project is to support and develop on-site research skills and to strengthen collaboration between countries. Therefore, the health-economic evaluations will be carried out locally at each of the sites. Central analysis will also be conducted for the pooled dataset of 900 (5 × 180) participants. The pooled data will be analyzed using mixed linear models with random effects both at the patient and site levels (equivalent to individual participant data meta-analysis) or alternatively with design-based analysis for the data of participants clustered at sites. The pooled data analysis, which has greater statistical power to detect significant effects, will include WHODAS functioning (on the continuous scale), as well as treatment response (dichotomized) and EQ-5D QALY gains. Finally, the pooled data will allow for multilevel modelling of net monetary benefits as the outcome of interest, with net benefits defined as NB = E*λ- C, where NB represents the net benefits, E represents the effects, λ represents a varying willingness-to-pay value (in euro) for gaining one unit of E, and C represents the costs required for generating that one unit health gain.

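### Prognostic covariates beyond baseline WHODAS and baseline cost enter only when an imbalance is seen; one fixed set for all five trials would be a cheap improvement

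*Protocol article*

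**What the plan says.** All references are to the protocol article.

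- **Allocation** (Randomization and Masking): "Simple randomization with 1:1 allocation will be applied", done separately at each site, with no stratification factor named.
- **Population** (Recruitment; Eligible Participants): patients are "recruited from the population being treated by specialized inpatient and outpatient mental health services". Each trial admits both first entries and readmissions, across several diagnoses.
- **Extra covariates** (Cost-Effectiveness Analysis, second step): baseline characteristics are examined for imbalance in variables strongly correlated with the outcome. "If this is the case, such variables will be used as covariates to make adjustments for the baseline imbalances". If there are many, the plan moves to inverse propensity score weighting.
- **Covariates already planned** (same section, fifth step): the SURE models adjust for baseline WHODAS and baseline cost, or are weighted by propensity scores as needed.
- **Reach of the rule**: the Cost-Utility Analysis section takes over the same methods. The Analysis of Pooled Trial Data section says "the health-economic evaluations will be carried out locally at each of the sites" and adds: "Central analysis will also be conducted for the pooled dataset of 900 (5 × 180) participants".

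**The concern.** A baseline variable that predicts the outcome reduces residual variance whether or not the arms differ on it. A rule that admits it only when the arms look different discards that gain whenever they look alike. It also makes the model a product of the data, since both the imbalance and, possibly, the correlation with outcome are judged in the trial's own sample. Imbalance is a chance event in each trial, so five trials following one rule will tend to adjust for different things. Country results will be reported side by side, and part of any difference between them could then come from the models.

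Recruitment setting, entry type and diagnosis are plausible predictors of both cost and functioning, and simple randomization leaves their balance to chance.

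**Working it through.** **1. The plan's own figure.** Sample Size Calculation gives d = 0.33, two-sided α = 0.05, power 0.80, and correlations r01 (0.3 to 0.5) and r12 (0.2 to 0.4). The ANCOVA formula is n per arm = 2(1.960 + 0.842)² × [(1 + r12)/2 − r01²] / 0.33². In the worst cell (r01 = 0.3, r12 = 0.4) the bracket is 0.70 − 0.09 = 0.61, so n = 15.70 × 0.61 / 0.1089 = 87.9, that is 88. All nine cells of Table 1 reproduce. At 90 per arm the standard error is √(2 × 0.61/90) = 0.1164 and the power is Φ(0.33/0.1164 − 1.96) = 80.9%. The baseline adjustment matters: with r01 set to 0 the same cell needs 101 per arm, and power at 90 is 75.4%.

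**2. What further covariates could add.** The article gives no R² for them, so this is an assumption. Residual variance becomes 0.61 × (1 − R²):

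| Added R² | Power at 90 per arm | n per arm for 80% |
|---|---|---|
| 0 | 80.9% | 88 |
| 0.05 | 82.8% | 84 |
| 0.10 | 84.8% | 80 |
| 0.20 | 88.7% | 71 |

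**3. What the trigger rule gives up.** Simulation, 4,000 trials per scenario: N = 180, simple randomization, continuous outcome, baseline always in the model, four extra covariates, effect 0.33. Extra variance is (SD triggered / SD fixed)² − 1.

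| Added R² | Trigger | SD fixed | SD triggered | Extra variance | Power fixed | Power triggered |
|---|---|---|---|---|---|---|
| 0.05 | SMD > 0.1 | 0.1134 | 0.1135 | 0.2% | 80.3% | 79.3% |
| 0.05 | SMD > 0.2 | 0.1157 | 0.1164 | 1.2% | 81.0% | 80.0% |
| 0.05 | p < 0.05 | 0.1185 | 0.1197 | 2.0% | 81.5% | 80.5% |
| 0.10 | SMD > 0.1 | 0.1120 | 0.1124 | 0.7% | 82.6% | 81.0% |
| 0.10 | SMD > 0.2 | 0.1086 | 0.1104 | 3.3% | 83.4% | 80.8% |
| 0.10 | p < 0.05 | 0.1131 | 0.1159 | 5.0% | 82.5% | 79.3% |
| 0.20 | SMD > 0.1 | 0.1079 | 0.1087 | 1.5% | 86.8% | 84.0% |
| 0.20 | SMD > 0.2 | 0.1054 | 0.1091 | 7.1% | 87.5% | 82.4% |
| 0.20 | p < 0.05 | 0.1086 | 0.1160 | 14.1% | 86.4% | 80.2% |

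Over triggers of 0.10 to 0.25 SD the extra variance is roughly 0 to 12%. A p < 0.05 trigger, which corresponds to an SMD of about 1.96 × 0.149 = 0.29, goes slightly beyond that at R² = 0.20. Power falls by about 1 to 6 points. Part of that loss arises because the model's standard error shrinks too little: at R² = 0.20 with trigger 0.2 it averages 0.1156, against a true SD of 0.1091.

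**4. Type I error.** With no effect, the mechanically applied rule rejected in 3.7% to 5.4% of runs.

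**5. Will the five models agree?** The SMD of one covariate has standard error √(2/90) = 0.149, so q = P(|SMD| > 0.2) = 0.18. All five trials treat that covariate alike with probability q⁵ + (1 − q)⁵ = 0.000 + 0.371 = 0.371. With k independent candidates (assumed) this is raised to the power k.

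| Trigger | q | One covariate | k = 3 | k = 5 |
|---|---|---|---|---|
| SMD > 0.1 | 0.50 | 0.063 | 0.0% | 0.0% |
| SMD > 0.2 | 0.18 | 0.371 | 5% | 0.7% |
| p < 0.05 | 0.05 | 0.774 | 46% | 28% |

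Even under one common threshold, different covariate sets are more likely than not.

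**The case against.** The best reply is that the important adjustment is already in place. Baseline WHODAS and baseline cost are planned covariates, Table 1 relies on nothing further, and the worst cell still has 80.9% power. What is lost is therefore a gain forgone, not a shortfall against the stated power. That stands, and it limits the size of the point. Baseline cost may also absorb part of the difference between inpatients and outpatients. A list of candidates or a threshold could well sit in the central study protocol. Their absence from an article is no fault, but a list would not change a rule that selects on observed imbalance.

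Four stronger readings are tempting and are not supported:

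- *Unmasked local teams choose the covariates.* A reader might infer this from local analysis and the lack of masking. The masking statement concerns clinicians and patients, the Data Handling section describes a central study protocol, and no text says who selects covariates. The central pooled analysis need not inherit five models.
- *The rule inflates false positives.* Picking the smallest p-value over 16 models would give about 9% to 14%, but the plan selects on baseline imbalance, and that gives about 4% to 5%.
- *Unstratified allocation is itself a defect.* A factor with 50% prevalence differs by 10 percentage points or more in about 18% of trials, and in at least one of five with probability 1 − 0.82⁵ = 0.63. This is chance variation already reflected in the standard error. Unequal arms cost little: at 77 and 103, the 95% limits, power is 80.1%.
- *The precision loss is about a third.* That needs a comparison model without baseline and four covariates with a joint R² of 0.36, neither of which is this plan.

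**Conclusion.** The point holds in limited form and is a cheap improvement. The article states the rule, so this is not a detail left to another document. For covariates beyond baseline WHODAS and baseline cost, it costs roughly 0 to 12% in variance, or about 1 to 6 power points, with the upper end of the power loss reached under a p < 0.05 trigger. It lets the data choose the model, and it makes differing country models likely. The optional switch to weighting means that even the planned baseline adjustment could be replaced after looking at the data.

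The figures rest on an assumed added R² of 0.05 to 0.20, independent candidate covariates, and continuous WHODAS in the worst cell of Table 1. The economic analyses use dichotomized response, QALYs and costs, for which the article gives no variance inputs, so the size there is not known.

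**What to change.** Replace the second step with one prespecified covariate set, used in all five trials and in the pooled model regardless of observed balance:

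- baseline WHODAS
- baseline cost
- recruitment setting (inpatient or outpatient)
- entry type (first entry or readmission)
- diagnostic group

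Report baseline imbalance descriptively. Keep imbalance-driven adjustment and propensity weighting as sensitivity analyses only, and remove weighting as an as-needed alternative in the fifth step. Let all sites run the same analysis code, fixed before follow-up data are compared by arm.

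The cost is wording plus four or five degrees of freedom out of 180. Entry type and diagnosis are needed to establish eligibility, and setting should be known from where the patient was recruited; that all three are recorded in usable form is an assumption. Allocation need not change, which matters because 91 + 165 + 180 + 197 + 190 = 823 participants were already enrolled when the article was accepted.

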### Sample Size Calculation

Each of the trials is well powered with 90 participants per randomization group (n=180 in total) to detect a clinically relevant effect (mean standardized difference, *d*) of ≥0.33 as statistically significant (at α≤.05, two-tailed) with a power (1-β) of ≥0.80 when the primary outcome (WHODAS personal and social functioning) is evaluated in a baseline-adjusted analysis of variance or similarly specified regression model.

More specifically, the power calculation is carried out with the sample size procedure of Stata (Stata Corp, College Station, Texas, USA) (*sampsi* [13]) assuming that the effect evaluation of functioning would be carried out in a baseline-adjusted analysis of covariance (ANCOVA) with one baseline measurement and two follow-ups. We had to make assumptions about the strength of the correlation of functioning between *t_0_* and *t_1_* and between *t_1_* and *t_2_* (denoted as *r_0,1_* and *r_1,2_*, respectively). The WHODAS 2.0 has a high 1-week test-retest reliability of *r_0,1_*=0.98 [14], but the correlation between *t_0_* and *t_1_* will be lower when the measurements are further apart (12-month time interval between *t_0_* and *t_1_*). Hence, we assumed that *r_0,1_* would be in the more modest range of 0.30 to 0.50. Regarding the strength of the correlation of personal and social functioning between *t_1_* and *t_2_*, we made a similar assumption, but expect that this correlation will be weaker still (ie, in the range of 0.20 to 0.40). The size of these correlations is important because they affect the required sample size. For this reason, the sample size calculations were repeated for the likely range of *r_0,1_* and *r_1,2_*. Table 1 shows the required sample size (per arm) for varying *r_0,1_* and *r_1,2_* values.

**Table 1 table1:** Required sample size per condition for varying *r_0,1_* and *r_1,2_* values.

*r_1,2_* ^a^	*r_0,1_* ^b^		
	0.3	0.4	0.5
0.2	74	64	51
0.3	81	71	58
0.4	88	78	65

^a^Correlation of functioning between 12 months after baseline (*t_1_*) and 18 months after baseline (*t_2_*).

^b^Correlation of functioning between baseline (*t_0_*) and 12 months after baseline (*t_1_*).

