## Discussion

### General Considerations

This study will examine the cost-effectiveness of recovery-oriented community mental health care for patients with severe mental disorders (the intervention implemented in the RECOVER-E project) compared with CAU in Bulgaria, Croatia, Macedonia, Montenegro, and Romania. Health-economic evaluations will be conducted alongside hybrid effectiveness-implementation trials at each of the five sites. In addition, a pooled analysis will be performed combining all trial data. It is hypothesized that the shift toward deinstitutionalization using a locally adapted form of flexible assertive community treatment results in the reduction of health care costs by avoiding expensive emergency care or psychiatric hospitalization. At the same time, this intervention has a focus within service delivery on recovery goals, which is hypothesized to contribute to a greater sense of societal role fulfilment and participation in society among people with severe mental illness. It is not unlikely that patients receiving community care will show larger improvements in WHODAS personal and social functioning and EQ-5D health-related quality of life as compared with patients treated in hospital-based mental health care services.

Given the nature of the intervention, a pragmatic approach is chosen to implement and evaluate community mental health services. While this may affect internal validity (eg, due to the lack of allocation concealment and masking), the corresponding results may be more generalizable and applicable to routine practice settings [31]. Moreover, the proposed methodology includes some methodological solutions to combat threats to the internal validity of the trials (eg, inverse propensity score weighting when randomization appears to be suboptimal).

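### The inverse propensity weights do not say which arm p refers to; under the usual definition they are reversed and would roughly double baseline imbalance

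*Protocol article*

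**What the plan says.** The second step of the Cost-Effectiveness Analysis section compares baseline characteristics between arms and looks for imbalance in prognostic variables. The first response is ordinary adjustment: "If this is the case, such variables will be used as covariates to make adjustments for the baseline imbalances". Weighting is the second response: "In the unlikely scenario where many potential confounders are found", inverse propensity weights are used instead, "with w=1/p in the control group and w=1/(1-p) in the experimental group". The score p is to come from a logistic model and is explained as "the likelihood that a participant is in one condition rather than the other". Neither the condition nor the event modelled is named.

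In the fifth step, the SURE models for costs and effects are adjusted for baseline WHODAS and baseline cost, or are "weighted with inverse propensity scores as needed". The Cost-Utility Analysis section adopts the same methods. General Considerations in the Discussion offers "inverse propensity score weighting when randomization appears to be suboptimal" as an example of how threats to internal validity will be met.

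**The concern.** An inverse probability weight must use the probability of the arm the patient is actually in. An analyst who codes CMHC as 1, fits the logistic model and saves the fitted probability has p = Pr(CMHC). Applying the printed line to that p gives every patient the weight belonging to the other arm. The correction would then work backwards, and only in data sets where imbalance had already been found.

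Two features of the plan add to the stake. The fifth step words weighting as an alternative to adjustment for baseline WHODAS and cost, so nothing assures that covariates would offset a reversed weight. And the section on pooled data has the evaluations run locally at each site as well as centrally. Sites could therefore code p differently and make opposite adjustments from the same sentence.

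**Working it through.** **Inputs.** The weights and the description of p are from the Cost-Effectiveness Analysis section, second step. Allocation is from Randomization and Masking: "Simple randomization with 1:1 allocation will be applied". There are 90 patients per arm (Sample Size Calculation). The yardstick for size is the target difference, d "of ≥0.33 as statistically significant (at α≤.05, two-tailed) with a power (1-β) of ≥0.80". My assumption is a baseline covariate that is normal with unit SD in each arm, with means d SD apart.

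**The plan's own figures.** The protocol gives no numerical result for the weights. Its largest sample size (r01 = 0.3, r12 = 0.4) reproduces: 2 × (2.8016/0.33)² × [(1 + 0.4)/2 − 0.3²] = 2 × 72.07 × 0.61 = 87.9, so 88 per arm. This has no bearing on the weights beyond confirming 0.33 SD as the scale.

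**Step 1, algebra.** Let f0 and f1 be the covariate densities in CAU (mean 0) and CMHC (mean d). With 1:1 allocation and p = Pr(CMHC | x), p/(1−p) = f1/f0.

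- Matched weights: CAU gets 1/(1−p) = 1 + f1/f0 and CMHC gets 1/p = 1 + f0/f1. Both weighted densities become f0 + f1, both means are d/2, and the difference is 0.
- Printed weights with this p: CAU gets 1/p, so its density becomes f0 + f0²/f1. The second term is a normal with mean −d and mass exp(d²). CMHC gets 1/(1−p), so its density becomes f1 + f1²/f0. The second term has mean 2d and the same mass.
- With E = exp(d²), the weighted difference is (d + 2dE)/(1 + E) − (−dE)/(1 + E) = d(1 + 3E)/(1 + E). For small d this is 4d/2 = 2d.
- Printed weights with p = Pr(CAU): these are the matched weights, and the difference is 0.

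**Step 2, numbers.** For d = 0.3, E = exp(0.09) = 1.0942 and 0.3 × 4.2825/2.0942 = 0.613. A simulated sample of 1,000,000 agrees to within sampling error (SD units):

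| d | Formula, p = Pr(CMHC) | Raw, simulated | Printed weights, p = Pr(CMHC) | Printed weights, p = Pr(CAU) |
|---|---|---|---|---|
| 0.1 | 0.200 | 0.104 | 0.204 | 0.004 |
| 0.2 | 0.404 | 0.202 | 0.406 | 0.002 |
| 0.3 | 0.613 | 0.301 | 0.615 | 0.001 |
| 0.5 | 1.062 | 0.501 | 1.063 | 0.000 |

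**Step 3, trial size with a fitted p.** I used 2,000 simulated trials of n = 180 with simple randomization and a fitted logistic model, keeping those with raw imbalance above 0.2 SD. With p = Pr(CMHC), the ratio of weighted to raw imbalance had median 2.03 with one covariate (5th to 95th percentile 1.99 to 2.09) and 2.07 with five (2.00 to 2.21). With matched weights the median ratio was 0.00 (−0.09 to 0.08 with five covariates).

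**Step 4, effect on the outcome difference.** On a continuous outcome with no other adjustment, bias is about the covariate-outcome correlation times the imbalance. The protocol's assumed range for baseline with 12-month functioning, 0.30 to 0.50, serves as an illustration. For a raw imbalance of 0.30 SD:

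- Unweighted: 0.3 × 0.30 = 0.09 to 0.5 × 0.30 = 0.15 SD.
- Printed weights with p = Pr(CMHC): 0.3 × 0.613 = 0.18 to 0.5 × 0.613 = 0.31 SD, against a target of 0.33.
- Matched weights, or the printed weights with p = Pr(CAU): about 0.

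**Step 5, how often.** At 90 per arm the standard error of a chance imbalance is √(2/90) = 0.149 SD. A difference of 0.30 SD in a given covariate is thus about a 2-standard-error event, near 4% two-sided. In the pooled set of 900 the standard error is √(2/450) = 0.067 SD.

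**The case against.** The strongest reply is that no swap is proved. The protocol does not say that p is the probability of CMHC, and putting 1/p beside the control group is itself some evidence that the probability of control was meant. On that reading the formula is exactly right. This stands: a reader might infer that the weights are simply wrong, and the text does not support that. What remains is that one reading removes imbalance, the conventional one doubles it, and nothing in the document chooses between them.

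Reach is also limited. Covariate adjustment comes first, weighting is reserved for a scenario called unlikely, and the Discussion cites it only as one example of a safeguard. That stands too, and it lowers the severity. It does not remove the point, because the formula operates only once imbalance has been found.

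A reader might also infer that covariates enter only after imbalance has been seen. That does not hold. The fifth step already plans adjustment for baseline WHODAS and cost, and the sample size sections assume a baseline-adjusted analysis.

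Finally, the bias figures depend on assumed correlations and a continuous outcome, not on the planned SURE models of cost and binary response. Simulations that weight every trial would not describe this plan, which weights only in the fallback case. The doubling of imbalance depends on neither.

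**Conclusion.** The point holds in conditional form. The protocol prints a definite weighting rule and leaves p undefined. If p has its usual meaning, Pr(CMHC | baseline covariates), the weights are reversed and baseline imbalance becomes about 2.0 to 2.1 times as large instead of falling to about zero. If p = Pr(CAU), there is no error beyond the missing definition.

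Harm requires that many imbalanced prognostic variables are found, that weighting is used in place of covariates, and that p is coded as the probability of CMHC. When all three occur, both the cost-effectiveness and the cost-utility results are affected. The size rests on normal covariates and 1:1 allocation. The translation into 0.18 to 0.31 SD of outcome bias further assumes a 0.30 SD imbalance and correlations of 0.30 to 0.50. This should be fixed, but given its narrow trigger it is not a critical flaw.

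**What to change.** In the second step of the Cost-Effectiveness Analysis section, define p = Pr(CMHC | baseline covariates) from a logistic model with CMHC as the event, and set w = 1/p for CMHC and w = 1/(1−p) for CAU. Alternatively, state that p = Pr(CAU) and leave the formula as printed. Use the same definition at every site and in the pooled analysis.

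In the fifth step, say that baseline WHODAS and baseline cost stay in the SURE models as covariates when weights are used, so that weighting adds to baseline adjustment and does not replace it. Tabulating balance before and after weighting would expose a coding reversal at once.

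The cost is a sentence or two of analysis text. No data, patients or visits are affected.
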